#### Participants

Fifty adults with mild to moderate intellectual disabilities aged 18 years and over, and who are known to professionals within the intellectual disabilities services as possibly having an alcohol problem, will be eligible to be referred to the study. Each participant should have a carer or family member prepared to accompany them to their sessions and complete the study instruments. Further justification for the sample size is available from http://www.nihr.ac.uk/CCF/RfPB/FAQs/Feasibility_and_pilot_studies.pdf.

Following informed consent, the participants will be assessed with the Wechsler Abbreviated Scale for Intelligence (WASI) [23] to ascertain their level of cognitive functioning (unless results from a previous cognitive assessment are available).

#### Recruitment

Recruitment of participants will be achieved through contacts and liaison with the intellectual disability services in the participating areas. Supported accommodation and social clubs in those areas will also be approached. Research assistants will work to increase publicity of the study by presenting it at all team meetings and submitting adverts for the study in organisational newsletters. Participant flow to the study is shown in Figure 1.

**Figure 1 Fig1:**
[figure not shown]
**Recruitment flow diagram.**

#### Inclusion criteria

Inclusion criteria are as follows:AUDIT score >8 (providing the sum of questions 4, 5 and 6 is below 9). A score of 8 and above indicates hazardous or harmful drinking [24]. Questions 4, 5 and 6 specifically assess symptoms of dependence. The National Institute of Care and Clinical Excellence (NICE) [19] advises a reduction of scores in particular populations who may have lower prevalence of AUD, such as older people, females, and younger people. Local data, however, suggests that the prevalence of AUD in adults with mild/moderate intellectual disability in contact with services based on an AUDIT cut off of 8 is 22.5%, which is similar to the prevalence in the general population [4]. Therefore, a decision was made to adopt the same cut-off AUDIT score as in the general population.Residents in the area within the last 12 months.Full Scale IQ <70 (+/− 5% CI), which is the range for mild and moderate intellectual ability.

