## Abstract

**Background:**

There is some evidence that people with intellectual disabilities who live in the community are exposed to the same risks of alcohol use as the rest of the population. Various interventions have been evaluated in the general population to tackle hazardous or harmful drinking and alcohol dependence, but the literature evaluating interventions is very limited regarding intellectual disabilities. The National Institute for Health and Clinical Excellence recommends that brief and extended brief interventions be used to help young persons and adults who have screened as positive for hazardous and harmful drinking. The objective of this trial is to investigate the feasibility of adapting and delivering an extended brief intervention (EBI) to persons with mild/moderate intellectual disability who live in the community and whose level of drinking is harmful or hazardous.

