## Background

Alcohol is the most commonly used substance worldwide and contributes substantially to mortality, psychiatric and physical health morbidity and causes increased disease burden [1,2]. Despite the sparse literature regarding substance misuse in people with intellectual disabilities (characterised by an Intelligence Quotient (IQ) less than 70, developmental delay and adaptive deficits), there is increasing interest in studying such problems in this population. This is because most now live in the community and are more likely to be exposed to substances [3,4]. United Kingdom and United States population-based studies indicate that the prevalence of substance misuse in people with intellectual disabilities ranges from 0.5% and 2.5%, respectively, to as high as 25% for any substance in clinic samples [4-6]. Approximately 5% of the youth in drug and alcohol services have a degree of intellectual disability [1]. The most common substance that people with intellectual disabilities tend to use is alcohol, followed by cannabis and cocaine [2]. Aetiological factors that have been postulated to contribute to substance misuse in people with mild to moderate intellectual disabilities include hyperactivity, lack of assertiveness, low self-esteem, susceptibility to peer pressure, desire for social acceptance, social isolation, early onset of drinking and lack of example setting in childhood [1]. Substances may also be taken as a maladaptive way of relieving stress or developing relationships within local communities [7,8]. Those most at risk are young males with a mild intellectual disability or borderline intelligence who live independently and are less likely to engage in activities and/or to experience mental health problems [1].

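### The AUDIT entry rule is written as above 8, but its own justification and stated decision use a cut-off of 8 and above

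*Protocol article*

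**What the plan says.** Under Inclusion criteria, the protocol article's first requirement is "AUDIT score >8 (providing the sum of questions 4, 5 and 6 is below 9". The reasons for that threshold follow within the same criterion:

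- "A score of 8 and above indicates hazardous or harmful drinking".
- Local data on service users with mild or moderate disability are cited, and the prevalence of alcohol use disorder is reported as follows: "based on an AUDIT cut off of 8 is 22.5%, which is similar to the prevalence in the general population".
- As a result, "a decision was made to adopt the same cut-off AUDIT score as in the general population".

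The Abstract (Background) describes the target group as "persons with mild/moderate intellectual disability who live in the community and whose level of drinking is harmful or hazardous". Under Aims and objectives, the number of eligible participants and the recruitment rate are among the quantities the trial will measure to inform a multicentre trial.

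The IQ criterion in the same list sets Full Scale IQ below 70 with a plus-or-minus tolerance written as "5% CI), which is the range for mild and moderate intellectual ability". The tolerance is not explained. The Background section characterises intellectual disability by "Intelligence Quotient (IQ) less than 70", with no tolerance.

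**The concern.** The operative rule and its rationale point to different thresholds. A research assistant who applies the rule literally refuses a candidate scoring 8. One who follows the rationale accepts the same candidate. The article's own definition puts that candidate inside the target population.

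What is at stake is the feasibility output. The eligible count and the recruitment rate are meant to carry forward to the design of the larger trial, and both depend on which threshold was applied. Someone refused at 8 and not recorded cannot be restored to the count afterwards.

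**Working it through.** The article reports no figure for this point that could be reproduced, so the check compares the sets of scores that each statement admits. Two assumptions are made: AUDIT totals are whole numbers, and no item scores below zero.

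**Step 1: the total score.**

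| Source in Inclusion criteria | Threshold | Is a score of 8 included? |
|---|---|---|
| Entry rule | above 8, so 9 or more | No |
| Definition of hazardous or harmful drinking | 8 and above | Yes |
| Cut-off behind the 22.5% prevalence | 8 | Yes, on the definition above |
| Stated decision | same cut-off as the general population, given as 8 | Yes |

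The set {8, 9, 10, …} minus the set {9, 10, …} is {8}. The disagreement is exactly one score.

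**Step 2: does the dependence proviso settle it?** The rule also requires that questions 4, 5 and 6 sum to less than 9. If the total is 8, those three items can sum to at most 8, and 8 < 9. The proviso therefore never removes anyone with a total of 8. Only the total-score rule decides that case.

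**Step 3: effect on the eligible count.** Let E be the number of screened people who meet every other criterion and score 9 or more, and let n₈ be the number who meet every other criterion and score exactly 8.

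- Count under the written rule: E.
- Count under the adopted cut-off: E + n₈.
- Share of eligible people lost: n₈ / (E + n₈).

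The article gives neither E nor n₈, nor any AUDIT distribution from which to derive them, so the share cannot be computed.

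**Step 4: the IQ tolerance, as a clarification.** The wording allows several readings:

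- As a percentage of 70: 0.05 × 70 = 3.5, so the limit is 66.5 or 73.5.
- As IQ points: 70 ± 5, so the limit is 65 or 75.
- As a confidence interval: the limit depends on the test's measurement error and on which bound is compared with 70. Neither is stated.

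**The case against.** The strongest reply is that this is a one-character slip in a condensed article, with the intended meaning plain from the surrounding text. The rationale names the cut-off, and nothing shows that any site has refused a candidate at 8. The consequences are also limited. The article plans no hypothesis testing, and no sample-size or power figure rests on this threshold. Eligibility is settled before randomisation and applies to both arms alike, so the comparison is not biased.

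Much of this stands, and it limits the severity. It does not remove the point. The sentence that contains the slip is the rule that decides who enters. A fuller protocol might print it correctly, but that would not reconcile the rule and rationale printed here.

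On IQ, the objection largely succeeds. The mild and moderate categories, and the exclusion of severe to profound disability, partly bound the population. The handling of test error is detail that a full protocol may define. The Background wording is a general description and not an entry rule, so it does not contradict the criterion.

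**Conclusion.** The criterion is wrong as written: it contradicts its own justification at an AUDIT score of 8. It affects the eligible count and the recruitment rate at that one score, by an amount the article does not allow to be estimated. This is a minor to moderate fault of internal consistency. The conclusion rests on the article's own sentences and on AUDIT being scored in whole numbers without negative items.

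A reader might infer more than the document supports:

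- **That the thresholds fail to define the population.** The AUDIT rule is misplaced by one score at the boundary and is otherwise usable.
- **That the eligible count can no longer be compared with the 22.5% prevalence.** No such comparison is planned. The figure only justifies not lowering the cut-off. The eligible count is in any case filtered further by the dependence proviso, recent treatment and the need for a willing carer.
- **That the three areas will apply different IQ limits.** Nothing in the article shows this, and the research assistants are to be trained by the research team.
- **That a percentage of candidates lost, or a widening of the IQ pool, can be stated.** Either figure would need a score distribution that the article does not give. A general-population IQ curve would not describe people recruited through intellectual disability services and related community settings.

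**What to change.** Reconcile the AUDIT criterion with the cut-off the article says it adopted, so that it reads as a score of 8 or more, leaving the proviso on questions 4, 5 and 6 as it is. Record the date of the change. In the screening log, identify anyone already refused because of a score of exactly 8, so that the eligible count and recruitment rate can be reported on one definition for the whole recruitment period.

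As a secondary clarification, state what the tolerance on the IQ limit means: percentage, points or confidence interval, and in the last case which bound is compared with 70.

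The cost is an amendment to the wording and a log entry. No sample-size or analysis change follows. The small downside is that, because Trial status says recruitment is under way, the wording changes part-way through. The date and the log entries are there to deal with that.

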#### Exclusion criteria

Exclusion criteria are as follows:severe to profound intellectual disabilities.non-English speaking requiring interpreters.in receipt of treatment for alcohol related problems in the last 12 months.acute stage of severe and enduring mental illness.poly-substance misuse including alcohol where the illicit substance, for example, cocaine/heroin/cannabis is the main problem.

#### Trial arms

The trial arms are as follows:Intervention: EBI is modified as described in stage 1. It will be provided over five half-hour weekly sessions with a final one-hour session after eight weeks. It will be delivered by a trained therapist recruited from the NHS/private or third sector providing alcohol services in England. It is likely that the therapist may not have experience working with adults with intellectual disabilities; therefore, the research team members will provide training in the form of a one-day induction, including aspects of communication and how to overcome cognitive limitations in people with intellectual disabilities, interviewing techniques, use of the manualised treatment and guided reading to enhance clinical skills in working with this population. Furthermore, tapes of early treatment sessions will be reviewed by co-authors CK and KS. The therapist will be supervised regularly by CK, a consultant psychiatrist in addictions and trained in motivational interviewing.Treatment as usual: Service users with mild to moderate intellectual disabilities who are identified as having AUD usually receive little specific support [25]; however, if problems escalate to dependence, they may be referred and managed jointly with secondary substance misuse services. Therefore, they may be offered non-specific counselling on improving coping abilities, pharmacological interventions where there are comorbid mental health problems or to achieve abstinence, inpatient admission if required, encouragement to attend community services for alcohol disorders, social support and nursing input if they experience any physical signs of malnutrition or epilepsy and other alcohol-related morbidity.

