### Stage 2-Feasibility study

#### Design

This will be a single blind, randomised controlled trial of individual EBI delivered as an adjunct to usual care for alcohol use disorders (AUD). Fifty participants, randomised to either the intervention arm or usual care, will be assessed at baseline, two months and three months. Research assistants carrying out assessments will be blind to the trial arm to which the participants are allocated.

Finally, qualitative interviews will be carried out at three months (see stage 3 below).

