#### Instruments

Instruments used in the trial will include the following:AUDIT [24], which is a screening tool for identification of excessive drinking, an aid to brief interventions, and it has been used with people with mild to moderate intellectual disabilities. It will be administered at all treatment points.Readiness to Change Questionnaire (RCQ) [27], which has been shown to have good validity and reliability. It contains 12 statements that must be read to the person with mild to moderate intellectual disabilities. It will be administered at baseline and three months.Euro-QoL (EQ-5D-3 L); English version [28], which is a short questionnaire assessing general healthcare. This questionnaire has been used extensively in health research in the general population and more recently in studies of populations with intellectual disabilities. This will be administered at baseline and three months.Clinical Outcomes in Routine Evaluation (CORE-LD) [29], which is an adapted version of the instrument for people with intellectual disabilities and measures self-reported psychological distress. It will be administered at baseline and three months.Client Service Receipt Inventory (CSRI) [30], which is specifically adapted for the study to measure what services the client has been in receipt of in the past 6 months (for example, emergency room attendance, GP visits, benefits). It will be completed at baseline and three months for the previous three months. Data gathered by this tool will allow us to be more precise in recording the different services received by participants each study arm beyond the intervention and quantify the elements of ‘treatment as usual’.Sociodemographic details at baseline.

All instruments will be completed by research assistants in face-to-face assessments with participants and paid or family carers. These assessments will take place at a convenient location. AH and KS will train Research assistants in interviewing techniques for people with intellectual disabilities, how to assess capacity to consent to research and how to administer the study instruments.

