#### Randomisation and masking

Randomisation will be conducted by contacting an external researcher once the potential participant has consented to take part in the study and baseline data have been collected (class A method of randomisation). The research team statistician will generate the randomisation list. Any breach in blinding/unmasking, a common problem with single blind trials, will be monitored to ensure that the research assistants are not aware, as far as possible, to which group the individual was allocated. The researchers will make a note of which group he/she believes the participant has been allocated to for all participants and this will be compared to the actual allocations at the end of the study. The database management will be supervised by the PRIMENT Clinical Trials Unit and the study statistician GB.

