### Stage 3-Qualitative study

In order to assess the perceived acceptability and usefulness of the intervention, 50% of service user and carer dyads allocated to the EBI arm of the trial, will be interviewed at end of treatment (that is, 12 weeks). The interviews will be completed by the two service users who are supported to contribute to the study reference group (part of the trial management group), with support from the research assistants. Both service users and the research assistants will be trained in how to collect qualitative data and conduct the interviews. We will include participants who may have dropped out of treatment, if at all possible, in order to ascertain their perceptions of the intervention and their reasons for dropping out. Interviews will be audiotaped and analysed using content analysis and/ or thematic analysis [33,34].

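### On the best-fitting reading, EBI ends 0 to 1 week before the last AUDIT, and the EBI-only interview, supported by research assistants, falls at or before that blinded assessment

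*Protocol article*

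**What the plan says.** All references are to the Protocol article.

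- **Treatment schedule (Trial arms).** Of EBI: "It will be provided over five half-hour weekly sessions with a final one-hour session after eight weeks". The sentence does not say from which session the eight weeks run.
- **End of treatment (Stage 3).** Half of the service user and carer dyads in the EBI arm "will be interviewed at end of treatment (that is, 12 weeks". No starting point is given for the 12 weeks. Two service users conduct these interviews, with research assistants supporting them.
- **Assessments (Stage 2, Design).** Participants "will be assessed at baseline, two months and three months". The same section places the qualitative interviews at three months. The AUDIT is the primary outcome (Outcome measures) and is given at every time point (Instruments), so its last reading is at three months.
- **Masking (Stage 2, Design).** "Research assistants carrying out assessments will be blind to the trial arm to which the participants are allocated".
- **Order of events (Randomisation and masking).** Randomisation takes place "once the potential participant has consented to take part in the study and baseline data have been collected", so treatment cannot begin until some time after baseline.

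**The concern.** Two consequences follow if these times are applied as written.

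First, the last AUDIT sits almost on top of the planned end of treatment. A participant who starts late or postpones sessions can reach the three-month AUDIT before the final session, which is the longest of the six. Some slippage is plausible. Treatment starts only after baseline and randomisation. The first appointment has to be arranged with the therapist. On attendance the article says: "Each participant should have a carer or family member prepared to accompany them to their sessions". The Discussion itself expects people who are hard to reach and may not commit to treatment. The EBI arm's AUDIT would then mix people who had the full course with people who had not, and this trial is meant to supply the standard deviation and effect-size estimates for the definitive trial (Aims and objectives; Statistical analysis).

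Second, only EBI dyads are interviewed, so being due for an interview identifies the arm. Research assistants support the interviews, and research assistants collect the blinded three-month outcomes. If the interview comes first, the assessor can learn the allocation before reading the primary outcome, which is collected face to face.

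**Working it through.** **Inputs.** Sessions: five weekly half-hours, then one of one hour (Trial arms). End of treatment: 12 weeks (Stage 3). Assessments: baseline, two and three months (Design). Sample: 50 in two arms; 25 per arm is assumed, because the article states no allocation ratio.

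**1. Reproducing the 12 weeks.** Weekly sessions fall at weeks 0, 1, 2, 3 and 4 from the first. Eight weeks after the fifth session is 4 + 8 = 12, which matches Stage 3.

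**2. Slack to the last AUDIT.** Three months = 3 × 365.25 / 12 / 7 = 13.04 weeks. Two months = 8.70 weeks. Design and Stage 3 give three months and 12 weeks for the same interviews, so the two may be meant as one point; both values are shown.

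| Eight weeks counted from | Final session | Slack if three months = 13.04 weeks | Slack if three months = 12 weeks | Fits the 12-week end? |
|---|---|---|---|---|
| Session 5 (week 4) | week 12 | 1.04 weeks | 0 | yes |
| Session 1 (week 0) | week 8 | 5.04 weeks | 4 weeks | no |

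On the first row, the two-month AUDIT falls 12 − 8.70 = 3.3 weeks before the final session.

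**3. Treatment received if the AUDIT comes first.** Planned contact is 5 × 0.5 + 1 = 3.5 hours. Without the final session it is 2.5 hours, and 2.5 / 3.5 = 71%.

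**4. Illustration of how many could be affected (first row, 13.04 weeks).** The article gives neither a start delay nor a postponement rate, so both are assumed. Let d be the delay in weeks from the start of the assessment clock to the first session. Let k ~ Binomial(4, p) be the number of sessions 2 to 5 postponed, each costing a full week with no catch-up. The final session is then at 12 + d + k, and the AUDIT precedes it if d + k > 1.04.

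| d | Condition | p = 10% | p = 20% | p = 30% |
|---|---|---|---|---|
| 0 | k ≥ 2 | 5% (1.3 of 25) | 18% (4.5) | 35% (8.7) |
| 1 | k ≥ 1 | 34% (8.6) | 59% (14.8) | 76% (19.0) |
| 2 | any k | 100% (25) | 100% (25) | 100% (25) |

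For example, at d = 0 and p = 0.1: 1 − 0.9⁴ − 4 × 0.1 × 0.9³ = 1 − 0.6561 − 0.2916 = 0.052.

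**5. Order of interview and AUDIT.** Stage 3 puts the interview at 12 weeks and Design puts it at three months. Against an AUDIT at 13.04 weeks on the same clock, the interview is 1.04 weeks earlier or at the same time. Half of an assumed 25 EBI dyads is 12 or 13 participants. If the 12 weeks run from the first session and that session is more than about a week late, the interview falls after the AUDIT, but so does the final session. On the first row of step 2, then, an on-time participant faces the masking risk and a late one faces the incomplete-treatment risk.

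**The case against.** The strongest case on the other side has five parts.

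- **The 12-week end after the first session is inferred.** This stands. Trial arms alone also allows a final session at week 8, just before the two-month visit, with 4 to 5 weeks of slack. Only Stage 3 points to 12. If its 12 weeks run from baseline or randomisation, they may already include the lead time, and adding d would count it twice. But 4 + 8 uses all 12 weeks, so lead time fits only if the eight weeks run from session 1.
- **The start of the assessment clock is not stated.** This stands too. Baseline or randomisation is the natural reading, since the usual-care arm has no sessions. The service-use inventory gives only weak support: "It will be completed at baseline and three months for the previous three months" follows a sentence that refers to six months. If the clock starts at randomisation, the slack need not cover the step from baseline to randomisation.
- **Visit windows and rescheduling rules may be in the full protocol.** True, and their absence from an article is not criticised here. The point rests on the times that are stated.
- **The percentages are assumption, not evidence.** Correct. The row at d = 2 is fixed by construction, and a range of 5% to 100% shows only that the result is sensitive to short delays. Nor should the wording "It will be delivered by a trained therapist recruited from the NHS/private or third sector" be read as proof that one person covers all three areas.
- **Delayed delivery is something a feasibility trial should observe.** Also fair. There is no hypothesis testing, adherence is an objective, five of six sessions would still precede the AUDIT, and the as-randomised summary remains the right main summary.

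None of this answers the masking point. The article does plan to record the assessors' guesses of allocation and compare them with the truth, but that measures unmasking and does not prevent it.

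**Conclusion.** The point holds in a limited form. On the reading that fits both Trial arms and Stage 3, the last AUDIT falls 0 to 1 week after the planned end of treatment, so a delay of more than about a week puts it before the final session. On the alternative reading the slack is 4 to 5 weeks, at the price of a conflict with the stated 12-week end. How many participants would be affected cannot be known from the article.

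The order of interview and AUDIT is the firmer part. As written, an EBI-only interview supported by research assistants comes at or before the AUDIT that blinded research assistants collect.

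A reader might infer more, and the article does not support it:

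- That treatment certainly outlasts the primary assessment for many participants. The starting points are inferred, and the delays are assumed.
- That the AUDIT mean or standard deviation will be distorted. No size of distortion can be derived from what is given.
- That masking will be broken. The article does not say whether the same research assistant supports the interview and assesses that participant, so the risk is possible rather than certain.
- That the primary assessment must be moved now. Recruitment is under way (Trial status), and a later time for remaining participants only would split a sample of 50 between two primary-outcome times.

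**What to change.** 1. Keep the three-month assessment for all participants, timed from randomisation in both arms.
2. Hold the qualitative interview only after the participant's last AUDIT is complete and after the final session. For someone who has left treatment, hold it after the last AUDIT.
3. Record the date of every session against the date of the last AUDIT. Report how many EBI participants had the AUDIT before the final session, with the AUDIT mean and standard deviation for each group, alongside the as-randomised summary and not in place of it.

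The cost is a slightly later interview for some dyads, plus a descriptive split of about 25 people by something that happens after randomisation. That split gives small, non-randomised groups and should not be read as a comparison of treatment doses. No visit is added, and neither the treatment nor the primary outcome time changes.

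Do not move the primary assessment to week 16 in mid-trial. For the definitive trial a later assessment is worth considering. Under the same assumptions, an AUDIT at week 16 precedes the final session only if d + k > 4, which at d = 2 means k ≥ 3, or 0.4%, 2.7% and 8.4% for p = 10%, 20% and 30%. The session dates recorded here would replace those assumptions with data.
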